All the questionnaires used are presented in the *Measures* section. Participants will complete the questionnaires via a digital form divided into four parts using the Microsoft Forms platform. They will receive a link to voluntarily engage with the forms (the original versions of the project can be accessed at the following links: Part I, https://forms.office.com/e/PW6gAqWVqv (accessed on 3 June 2026); Part II, https://forms.office.com/e/t2hmcpz0Ts (accessed on 3 June 2026); Part III, https://forms.office.com/e/ghJkDLyEEj (accessed on 3 June 2026); and Part IV, https://forms.office.com/e/h6TBgmzM8a (accessed on 3 June 2026). Supervision and assistance from the study team members will be available throughout the process.

(c) Kinesiological assessment of functional capacity, including aerobic capacity, muscular strength, and flexibility, will be performed at the C.U.R.I.A.Mo. Participants will be supervised by kinesiologists specifically trained. Assessment sessions will be preceded by almost one training session to familiarize participants with the machines and the specific protocol of the test. The procedures were reported in the Measures section. Moreover, to objectively evaluate the PA habits, participants will be asked to wear an ActiGraph wGT3X-BT (ActiGraph LLC, Pensacola, FL, USA) for a week.

(d) Comprehensive postural evaluation, categorized into objective, instrumental, functional, and neuromotor examinations.

Initially, a static assessment of overall posture will be performed in an upright position on various planes, observing alignment of the head and neck, symmetry of shoulders and scapulae, spinal alignment and overhang, pelvic position, waist triangles, lower limb alignment, and foot support. The physical examination will be followed by an instrumental evaluation using a plumb line, Bunnel’s scoliometer, measuring tape, goniometer, podoscope, measuring rod, and sit-and-reach test. Barré’s vertical line will be used to determine ascending, descending, mixed, or disharmonious syndrome [57]. The examination will continue in various positions to assess localized or peripheral pain. Functional examinations will evaluate muscle elasticity, mobility, and trophic tone through anterior, lateral flexion, and global extension tests.

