Trophic tones will be assessed with isotonic and isometric evaluations of abdominal muscles, gluteus medius, minimus, maximus, and spinal extensors. Evaluation of spinal curve accentuations, inversions, or extensions, especially dorsal and cervical, will be conducted in the sagittal plane to identify alterations in head posture that may affect MIGs, including specific cervical. The postural examination will conclude with neuromotor tests: Fukuda and Romberg tests (simple, monopodalic, and sensitized) will be used to assess general proprioception and balance [57].

This assessment will be followed by specific tests to evaluate how muscle contracture or weakness, cervical stiffness or instability, and poor posture may influence chronic or episodic MIG, focusing on the neck and cervical-dorsal muscles.

(e) Gnathological assessment will be conducted in accordance with the international diagnostic criteria (DC)/TMD [58]. This involves a thorough medical history of the disorders, followed by an examination of two reference axes. AXIS I focuses on identifying isolated muscle pain, condylar-disk dislocations, arthralgia, or degenerative bone changes within the temporomandibular joints, whereas AXIS II explores the psychological factors that influence the progression of the pathology and chronic pain. Participants will undergo a 4-channel surface electromyography (Teethan) examination [59]. The Baiobit motion sensor will also be used to perform cervical ROM [60,61], balance, and gait tests to identify ascending or descending interference factors in TMD.

After the evaluation, participants will be randomly assigned to two groups: the control group (*n* = 100), comprising people with MIG in standard care; and the intervention group (*n* = 100), comprising people with MIG in standard care plus supervised EXE intervention. Only the second group will attend a supervised, mixed EXE intervention (phase 3).

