#### 2.2.4. Phase 4: The Follow-Up

All evaluations will be re-executed after six (T1) and twelve (T2) months from the start of the study. During follow-up appointments, we will update specific process variables, described below.

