#### 2.3.3. Phase 3: Self-Administered (Online) and Researcher-Administered Questionnaire Values

Headache progression, disabilities, allodynia, fear of movement related to headaches, and overall quality of life. Headache-related disability will be evaluated using the Migraine Disability Assessment Score (MIDAS) [64], and the Headache Impact Test-6 (HIT-6) scores [65]. The HIT-6 is a 6-item questionnaire used to assess the impact and severity of MIG.

The MSQoL questionnaire, version 2.1, validated in Italian by Raggi et al. [66], includes 14 items assessing the impact of MIG on daily functioning across three domains: role function-restrictive (RR), role function-preventive (RP), and emotional function (EF). Items are rated on a 6-point scale (“none of the time” to “all of the time”); raw scores are summed and transformed to a 0–100 scale, with higher scores indicating better quality of life.

Allodynia will be assessed using the Allodynia Symptom Checklist (ASC), a 12-item questionnaire developed by Lipton et al. (2008) [67], which evaluates the frequency of various allodynia symptoms associated with MIG attacks.

Pain-related fear of movement will be measured using the Tampa Scale of Kinesiophobia [68].

The participants’ perspective on changes in their pain condition will be evaluated using the Patient Global Impression of Change (PGIC) [69].

Health-related quality of life will be assessed using the SF-36 questionnaire [70], while overall well-being will be measured with the World Health Organization-Five Well-Being Index (WHO-5) [71].

Measurement of Sleep Quality, Sleep Time, and Circadian Rhythms.

Sleep onset, continuity, duration, sleepiness, and sleep-disordered breathing will be evaluated using the Sleep Scale from the Medical Outcomes Study (MOS) questionnaire [72].

Sleep quality will be assessed using the Insomnia Severity Index (ISI), developed by Bastien et al. in 2001 [73]. This is a self-assessment tool that evaluates sleep quality, the presence of insomnia, and its severity. It consists of five multiple-choice questions, with higher scores indicating a greater severity of insomnia.

Chronotype will be defined using the Morningness–Eveningness Questionnaire (MEQ-SA) created by Horne and Ostberg (1976) [74]. This self-assessment scale helps identify the participant’s circadian phenotype and consists of 19 multiple-choice questions. Higher scores indicate a morning chronotype, whereas lower scores indicate an evening chronotype.

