The Spielberger State-Trait Anxiety Inventory (STAI-Y) (Spielberger et al., 1983) [79] is a self-administered assessment that measures the level of anxiety symptoms. This scale consists of 40 multiple-choice questions that distinguish between state anxiety and trait anxiety.

The Mania Rating Scale (MRS) (Young, 1978) [80] is a self-administered tool that evaluates hypomanic and manic symptoms and their severity. It comprises 11 multiple-choice questions, where a higher score indicates increased symptom severity.

The Mood Disorder Questionnaire (MDQ) (Hirschfeld, 2002) [81] is a self-administered scale that assesses the likelihood of an individual being affected by bipolar disorder. It consists of 17 multiple-choice questions.

The Obsessive-Compulsive Inventory-Revised (OCI-R) (Foa et al., 2002) [82] is a self-administered rating scale that identifies and assesses the severity of obsessive–compulsive disorder. This scale contains 18 multiple-choice questions, with higher scores reflecting greater severity of obsessive–compulsive disorder.

Levels of PA and sedentary behavior. The International Physical Activity Questionnaire (IPAQ) short form [83] assesses PA levels (expressed in MET-hours/week) by studying time spent in different types/intensity PA subgroups (moderate, vigorous, walking) and sedentary activities (<1.5 METs) over the past 7 days [83]. It is a self-report questionnaire whose responses are used to calculate metabolic equivalent task (MET) minutes per week, which allows classification of participants into low, moderate, or high PA levels.Gnathological aspects pertinent to AXIS 1 and AXIS 2. Gnathological assessment will be conducted according to the DC/TMD framework, evaluating both Axis I (physical and clinical features) and Axis II (psychosocial and behavioral factors).

Axis I: general information, pain, and symptoms will be observed through the Demographic Questionnaire, the TMD Pain Screener [84], and the Symptom Questionnaire DC/TMD [84,85].ASSE II: pain intensity and disability will be assessed using the GCPS Chronic Pain Scale (CGPS 2.0 [86]); changes in functional limitation will be assessed using the Jaw Functional Limitation Scale (JFLS-8) [87]; severity of depression will be measured using the Patient Health Questionnaire (PHQ-4) [88]; and the frequency and quantification of jaw overuse behaviors will be assessed with the Oral Behavior List (OBC) [89].

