### 2.4. Statistical Analysis

The primary efficacy analysis will be performed in the intention-to-treat (ITT) population. The pre-protocol population consisted of all patients in the ITT population without major protocol deviations and will be used for the supportive analysis of the primary efficacy endpoint.

The quantitative data collected, organized into two distinct groups of subjects, will be presented in tables that include the mean and standard deviation. In addition, qualitative data will be represented through frequency distributions.

The primary endpoint (number of MIGs/month from baseline to 6 and 12 months) will be analyzed using a linear mixed-effect model (LMEM) with treatment group × time as the fixed effect and the baseline number of MIG/month value as the covariate.

For qualitative data analysis, the Chi-square test will be implemented.

The scores obtained from the evaluation scales will be correlated with the clinical parameters of the participants, when applicable, using the Pearson or Spearman correlation coefficients, contingent upon the distribution of the data.

In the case of individuals with MIG, a logistic regression analysis will be performed to investigate potential associations between psychopathological parameters and the response to headache treatment. Adherence to both PA and TPE will be incorporated as process variables in the analyses. Dietary adherence scores from the Mediterranean Diet Assessment Tool, Diet Risk Score, and food-headache diaries will be assessed longitudinally for their potential as predictors of migraine outcomes. Additionally, EXE adherence will be evaluated through attendance records and wearable device data.

Analyses will be limited to participants with complete data on different measurements. We hypothesized that missing data occur randomly into two group. We plan to gather additional information from participants who drop out.

Should the dropout rate exceed our projections, we will employ a regression model to impute the missing data.

The exploratory outcomes will be evaluated utilizing the same LMEM employed for the primary analysis, without adjustments for multiple comparisons. Conclusions will be derived from effect size estimates, specifically Cohen’s d, accompanied by a 95% bootstrap confidence interval (CI). Effect sizes will be systematically classified as small (d = 0.2), medium (d = 0.5), and large (d = 0.8).

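### The only test named for categorical data is a Chi-square, which leaves the baseline category and the class order unused for binary and ordered secondary outcomes

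*Protocol article*

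**What the plan says.** Section 2.4 covers categorical data in one sentence: "For qualitative data analysis, the Chi-square test will be implemented". It names no adjusted, ordinal or repeated-measures version. In the same section the primary endpoint "will be analyzed using a linear mixed-effect model (LMEM) with treatment group × time as the fixed effect", with the baseline value as covariate, and the exploratory outcomes get the same model. No model is named specifically for secondary outcomes.

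The opening of section 2 lists physical activity levels, postural parameters and temporomandibular variables as secondary outcomes. Parts of these are recorded as categories:

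- The activity questionnaire (section 2.3.3) "allows classification of participants into low, moderate, or high PA levels".
- In the gnathological assessment (section 2.2.2), "AXIS I focuses on identifying isolated muscle pain, condylar-disk dislocations, arthralgia, or degenerative bone changes".
- In the postural assessment (section 2.2.2), Barré's vertical line "will be used to determine ascending, descending, mixed, or disharmonious syndrome".

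On timing, section 2.2.4 says "All evaluations will be re-executed after six (T1) and twelve (T2) months from the start of the study". Each of these variables should therefore have a baseline value and two follow-up values.

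**The concern.** A Chi-square test of arm by category at one visit uses only the category at that visit. It ignores the category the participant was in before randomisation, which usually predicts the later one. It also treats low, moderate and high as three unordered labels. The same section already applies a baseline-adjusted longitudinal model to the primary and exploratory outcomes, and gives no reason for handling categories differently.

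What is at stake is power for secondary results on which section 3 states hypotheses. A null temporomandibular or activity-class result could partly reflect the test chosen rather than the intervention.

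**Working it through.** **No plan figure to reproduce.** The article states no rate, effect, correlation or power for any categorical outcome. Its sample size concerns headache days only. The one usable input is 100 per group with 30% anticipated dropout: 100 × (1 − 0.30) = 70 evaluable per arm. Everything else below is assumed. Tests are two-sided at 5%.

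**Step 1. Validity.** In simulations with no treatment effect, 70 per arm and two or three classes, the Chi-square test rejected in 4.7% to 5.7% of runs. The test holds its level, so the issue is efficiency alone.

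**Step 2. Binary outcome, weak to moderate tracking.** A normal latent variable was cut into two classes (50/50 or 30/70). Its baseline-to-follow-up correlation was 0.3, 0.5 or 0.7, and the latent effect 0.3, 0.4 or 0.47 SD. There were 1,200 runs per cell, so each power has a standard error of at most √(0.25/1200) = 1.4 points. The adjusted test was a linear regression on the class score with baseline-category terms, standing in for logistic regression. The gain over Chi-square at one visit was:

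| Correlation | 50/50 split | 30/70 split |
|---|---|---|
| 0.3 | −1.2 to 1.0 | 0.0 to 1.0 |
| 0.5 | 1.7 to 5.8 | 1.0 to 3.6 |
| 0.7 | 8.4 to 11.8 | 6.1 to 10.2 |

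The range is about 0 to 12 points.

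**Step 3. Binary outcome, stable condition.** Here 50% have the condition at baseline. In each scenario below, follow-up prevalence is 50% in control and 35% in intervention; for example, 0.5 × 0.85 + 0.5 × 0.15 = 0.50 and 0.5 × 0.65 + 0.5 × 0.05 = 0.35. In closed form,

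power = Φ{[|p1 − p2| − 1.96·√(2p̄(1 − p̄)/n)] / √[(p1(1 − p1) + p2(1 − p2))/n]}.

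With p1 = 0.50, p2 = 0.35, p̄ = 0.425 and n = 70, this is Φ[(0.15 − 1.96 × 0.0836)/0.0826] = Φ(−0.17), or about 43%. The simulation (2,000 runs) agrees:

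| Persistence / new cases, control | Same, intervention | Chi-square | Baseline-adjusted logistic | Gain |
|---|---|---|---|---|
| 75% / 25% | 55% / 15% | 45% | 55% | 10 |
| 80% / 20% | 60% / 10% | 43% | 60% | 17 |
| 85% / 15% | 65% / 5% | 43% | 68% | 25 |

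Steps 2 and 3 agree with each other. At 50% prevalence, persistence q corresponds to a latent correlation of sin[π(q − 0.5)], which is 0.71, 0.81 and 0.89 for the three rows. Step 3 begins where step 2 ends. Below that range, persistence of 65%, 60% and 55% gave gains of only about 5, 2 and 1 points.

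**Step 4. Three ordered classes.** The set-up is that of step 2, with equal thirds. Each cell gives the three latent effects in turn.

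| Correlation | Chi-square | Using order | Using order and baseline |
|---|---|---|---|
| 0.3 | 26.0 / 43.0 / 60.2 | 33.2 / 52.2 / 70.8 | 36.0 / 54.8 / 73.4 |
| 0.5 | 26.7 / 43.3 / 59.0 | 35.7 / 55.7 / 68.4 | 41.0 / 62.8 / 75.8 |
| 0.7 | 28.0 / 44.2 / 59.2 | 35.2 / 54.6 / 69.8 | 49.6 / 71.0 / 85.1 |

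Order alone gains 7.2 to 12.4 points. Order and baseline together gain 10.0 to 26.8. A separate simulation with odds ratios of 2.0 to 2.6 gave 46% to 77% for Chi-square against 57% to 84% using order, a gain of about 7 to 11. The overall range is about 7 to 27 points.

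**Step 5. Which part applies to which variable.** Section 2.1 admits only people below the WHO activity recommendation, so the baseline activity class probably varies little. For that variable the order-only gain of about 7 to 12 points is the more relevant one. Axis I findings are binary, so only steps 2 and 3 apply. The four postural syndrome types have no natural order, so no gain from order can be claimed.

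**The case against.** The strongest reply is that the sentence speaks of qualitative data, not of outcomes. It names no variable, visit or contrast, and it may be meant for sex, aura, dropout, questionnaire completion or adverse events, where Chi-square is suitable. The article is condensed, and models for secondary variables commonly sit in a statistical analysis plan. Activity is also measured in MET-hours and by accelerometer, and many postural and jaw measures are quantitative, so the categorical versions are not the only evidence in those domains.

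Much of this stands. The sentence does cover one-time tables, and for those it needs no change. The test is not wrong, and no categorical outcome was powered. But nothing in section 2.4 limits the sentence to descriptive tables, and it is the only named test that fits the categorical parts of the secondary outcomes. The article does not leave the method open; it names one.

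A fair caution also applies to the remedy. A four-class multinomial longitudinal model on about 140 people (2 × 70) would be over-built, which is why the fix below stops at binary and ordered outcomes.

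**Conclusion.** The point holds as one of efficiency for binary and ordered categorical secondary outcomes. With about 70 per arm, the power lost at a single visit is about 0 to 12 points for a binary outcome with weak to moderate tracking and about 25 for a very stable one. For three ordered classes it is about 7 to 27. These figures depend on assumed prevalences, class splits, correlations and effects, none of which the article supplies.

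Three stronger readings might be inferred, and the document does not support them.

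- **A general loss of 10 to 30 points.** This cannot be derived from the article. The loss can be near zero for a binary item that tracks weakly. A large figure from the Patient Global Impression of Change would need an assumed number of levels. That scale also has no baseline value and is not named among the secondary outcomes.
- **Inflated false positives from stacking the 6- and 12-month rows in one table.** Nothing in section 2.4 says the visits will be pooled.
- **Harm to the primary analysis.** The primary endpoint has its own baseline-adjusted mixed model and is untouched.

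**What to change.** Replace the sentence in section 2.4 with text along these lines: *Between-arm comparisons of binary and ordered secondary outcomes at 6 and 12 months will use logistic or proportional-odds regression, adjusted for the outcome's own baseline category. Both visits will enter one repeated-measures model with arm, visit and arm by visit, from which separate 6- and 12-month effects will be reported. Chi-square or Fisher's exact test will be used for nominal variables, such as postural syndrome type, and for one-time tables, such as dropout and adverse events.*

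The plan should also choose between a population-averaged (GEE) and a subject-specific (mixed) model. The two estimate different odds ratios, and ordinary GEE makes the stronger missing-data assumption, which matters with 30% dropout anticipated.

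The cost is a few sentences and no new data. Results become odds ratios that rest on a model assumption (proportional odds for ordered classes). Percentages by arm and visit can still be tabulated beside them.

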### 2.3. Measures

#### 2.3.1. Phase 1: Medical Assessment

Participants will be invited to complete an online questionnaire to collect information about age, sex, years of illness, presence (or not) of MIG aura, frequency of headache attacks (number of attacks per month), intensity of the MIG episodes (measured using a 10-point numerical rating scale), and number of headache attacks per month (tracked using diaries provided to the participant). Moreover, dose and type of symptomatic and prophylaxis drugs used monthly by participants will be recorded.

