#### 2.3.2. Phase 2: Anthropometric, Metabolic, and Dietary Assessment

The following data will be collected:Anthropometric and blood pressure measurements. Weight, body mass index (BMI), fat mass, lean mass, and basal metabolism will be assessed using an impedance platform (Tanita Body Composition Analyzer BC-420MA; Tokyo, Japan) or an air plethysmograph (BOD POD^®^ Composition System; COSMED Srl, Albano Laziale, Rome, Italy). Height and waist circumference will be measured using a portable stadiometer (Seca 213, Seca GmbH & Co. KG, Hamburg, Germany) and an automatically retractable measuring tape (Seca 201, Seca GmbH & Co. KG, Hamburg, Germany), respectively. Systolic and diastolic blood pressures will be recorded using a digital column sphygmomanometer designed for professional auscultatory blood pressure measurement (UM-101, A&D Medical, Tokyo, Japan).Hematobiochemical values. We will evaluate several parameters, including glycemia, glycated hemoglobin (also referred to as glycosylated hemoglobin or HbA1c), lipid profile (which encompasses total cholesterol, HDL, LDL, and triglycerides), CRP, and medium- to long-term coronary heart disease (CHD) risk scores.Dietary information. Participants will be given a seven-day food and headache diary (adapted from the American Migraine Foundation model [55]), reported in Figure 2, in order to provide a detailed and structured overview of EH and their potential relationship with MIG episodes. Participants will report their usual meal composition and timing, hydration, caffeine and alcohol intake, specific notes such as symptoms and signs (e.g., nausea, vomiting, and taking supplements), and potential food triggers, in addition to the MIG attack’s characteristics (onset, intensity, duration, and medication use). Attention will be given to identify potential dietary triggers such as alcohol, caffeine, processed meats, and food containing additives like glutamate. EH that may contribute to MIG onset or exacerbation will also be considered, such as prolonged fasting, irregular mealtimes, and inadequate hydration. In line with the latest review [62], participants will receive a brochure with nutritional tips focused on the point described above, as part of SC.

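### Diary-derived eating patterns are to serve as predictors of migraine although attacks can themselves disturb meals and fluids, and Section 2.4 gives no rule that separates the two directions

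*Protocol article*

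**What the plan says.** Section 2.4 (Statistical Analysis) names three sources for the dietary predictor analysis: "Dietary adherence scores from the Mediterranean Diet Assessment Tool, Diet Risk Score, and food-headache diaries will be assessed longitudinally". Two are separate questionnaires. The third is the diary, and the sentence gives all three the same role, ending with the words "food-headache diaries will be assessed longitudinally for their potential as predictors of migraine outcomes".

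Section 2.3.2 describes the diary. "Participants will be given a seven-day food and headache diary", and on it "Participants will report their usual meal composition and timing, hydration, caffeine and alcohol intake". The same form takes "specific notes such as symptoms and signs (e.g., nausea, vomiting, and taking supplements") and the attack's "characteristics (onset, intensity, duration, and medication use"). Eating behaviour is discussed in one direction only: "EH that may contribute to MIG onset or exacerbation will also be considered, such as prolonged fasting, irregular mealtimes, and inadequate hydration".

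The monthly count is described in Section 2.3.1 as "number of headache attacks per month (tracked using diaries provided to the participant"). The article does not say whether those diaries are the seven-day form. All evaluations are repeated at six months (T1) and twelve months (T2), according to Section 2.2.4.

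**The concern.** A participant who is nauseated or vomiting may skip a meal, eat late or drink little. On such a day the diary shows fasting, irregular meals or low fluids because of the attack. People with more attacks then collect more of these entries, and their score correlates with attack frequency even if eating never provokes an attack.

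Measuring longitudinally does not remove this. Attack frequency persists within a person, so someone with many attacks at T0 tends to have both a disturbed T0 diary and a high T1 count. The lagged association survives unless the T0 count is in the model.

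At stake is the reading of the diary data. Eating patterns could be reported as predictors of migraine when they are its consequences, and the Discussion says that the diary was designed to find temporal associations. The article does not mention the reverse direction.

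**Working it through.** The plan gives no figure to reproduce. The check has two parts: how often attack days fall in the diary week, and what follows if attacks disturb eating but eating has no effect on attacks.

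**1. Attack days in a diary week.** Inputs: entry frequencies of 8–14 or at least 15 attacks a month (Section 2.1) and a seven-day diary (Section 2.3.2). Assumptions: one attack day per attack, a 30-day month, independent days. Expected attack days = 7 × f/30. Probability of a week with none = (1 − f/30)^7.

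| f per month | Expected attack days | P(no attack day) |
|---|---|---|
| 8 | 7 × 8/30 = 1.9 | (22/30)^7 = 11% |
| 14 | 7 × 14/30 = 3.3 | (16/30)^7 = 1.2% |
| 15 | 7 × 15/30 = 3.5 | (15/30)^7 = 0.8% |

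Almost every diary mixes the two kinds of day.

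**2. Day-level simulation with no effect of diet.** 200 participants, seven days, 400 runs, frequency uniform on 8–22 days a month. Assumed: disturbed eating on 20% of attack-free days and on 20–60% of attack days, with and without carry-over to the next day and clustering of attacks. The simplest case can be checked by hand. At 40% against 20%, the same-day odds ratio is (0.4/0.6)/(0.2/0.8) = 2.7. At 60% it is (0.6/0.4)/(0.2/0.8) = 6.0. Carry-over lowers both.

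| Disturbed on attack days | Same-day odds ratio | r, weekly score with monthly frequency | Significant at 5% |
|---|---|---|---|
| 20% (no disturbance) | 1.0 | about 0 | 3–7% |
| 30% | 1.5–1.7 | 0.07–0.08 | 17–20% |
| 40% | 2.0–2.7 | 0.12–0.13 | 43–49% |
| 60% | 3.6–6.0 | 0.22–0.24 | 89–93% |

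Where attacks disturb eating, relating one day's eating to an attack on the next day still gives odds ratios of 1.03–1.80. Restricting the exposure to attack-free days gives 0.99–1.07.

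**3. Visit-level simulation with no effect of diet.** 140 participants (200 × 0.70, the planned 30% dropout), 1,500 trials per setting in the main runs, half at 8–14 and half at 15–24 attack days a month. Assumed meal skipping: 20–50% on attack days and 10–20% on other days. The persistence of frequency between visits is also assumed and was varied. The ranges cover all settings in which attack-day skipping is the higher.

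| Analysis | Significant at 5% |
|---|---|
| Same visit | 19–100% |
| Lagged to the next visit, earlier count not in the model | 13–90% |
| Lagged, adjusted for the count at the diet visit | about 5% |

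With equal skipping on both kinds of day, the same-visit rate is 5%. The adjusted rate rose to as much as 14% when the diary week lay outside the month over which the count was taken, because the count then captures the attacks of that week less well.

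**The case against.** The strongest reply is that Section 2.4 fixes no model, lag or covariates for this analysis, so the harmful versions are possibilities and not the stated plan. A full analysis plan could order diet and attacks correctly, and the diary records onset, so the data allow it. The only model for the migraine count in Section 2.4 already carries the baseline count. This stands in part. If that model were reused, T0 diet would be adjusted for the T0 count, but T1 diet predicting T2 would not be adjusted for the T1 count. The published sentence already gives the diary score the role of predictor, and nothing in the article guards against the reverse direction.

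Several stronger readings are tempting, and the documents do not support them:

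- A reader might infer that all the dietary scores are affected. The Mediterranean Diet Assessment Tool and the Diet Risk Score are separate questionnaires, and the argument does not reach them in the same way.
- A reader might infer that the diary also supplies the outcome count. The article does not say so, and seven days cannot by themselves give a monthly number.
- A reader might infer that a false result is certain. Its size depends on how often attacks disturb eating, which is nowhere given. The form asks about usual meals, and no fasting or hydration score is defined.
- A reader might infer that the trial's use of its dietary data fails as a whole. Dietary adherence is also a secondary outcome, and the diary also serves to identify individual triggers.

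The article is also cautious about causation: Section 3 says that no definitive evidence supports a direct causal link. That caution does not change the predictor analysis.

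**Conclusion.** The point holds for the diary-derived items. A same-visit analysis, or a lagged one without the earlier count, can report fasting, irregular meals or low fluids as predictors of migraine when they are consequences. With no true effect of diet, false-positive rates ran from little above 10% to nearly 100%, depending on the assumed disturbance rate and, for the lagged test, on persistence between visits. They were about 5% when attacks did not disturb eating, or when the count at the diet visit was in a lagged model (up to 14% if that count did not cover the diary week).

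This rests on one attack day per attack and on assumed disturbance rates. The direction and the remedy were the same in every setting where attacks disturb eating; the size is not known. The randomised primary comparison is unaffected. It is worth correcting because the change is small and the diary findings could otherwise be read backwards.

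**What to change.** In Section 2.4, for the dietary predictor analysis:

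1. Relate diet scores at T0 to the migraine count at T1, and scores at T1 to the count at T2. Adjust for arm and for the migraine count at the visit where diet was measured, preferably counted over a month that contains the diary week.
2. Report same-visit results as descriptive associations, not as prediction.
3. As a sensitivity analysis, recompute diary scores from eating before recorded attack onset, or from attack-free days.

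The third step should not be the main rule. An attack-free-days score discards eating that precedes an attack on the same day, which a trigger analysis needs. It also loses participants: at 24 attack days a month only 7 × 6/30 = 1.4 usable days remain and (24/30)^7 = 21% of people have none, against about 3–4% of the simulated sample overall. Under the complete-data rule in Section 2.4 those people would drop out of the analysis.

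The cost is a few sentences of analysis text and no new data. The small downside is that short-term effects within the same week are not claimed as prediction.
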